#### Surgical technique

Under spinal anesthesia, the patient is placed in a modified lithotomy position on the back, with legs spread apart on supports. During anesthesia, the patient is sitting. The needle is inserted between L3 and L4 space or L4 and L5 space. We usually use a bupivacaine solution 5 mg/ml for spinal anesthesia. No adjuvant medicaments are used. The operative field is treated with an antiseptic solution twice and draped. A complex of external and internal hemorrhoids or internal hemorrhoids only is excised with monopolar electrocautery or bipolar electrosurgery device. Hemorrhoid pedicle is tied with an absorbable polyfilament suture, and then the pedicle is crossed by monopolar or bipolar electrocautery. The wound is not sutured. One, two, or three nodes can be removed per procedure depending on the number of the enlarged hemorrhoidal nodes.

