### Baseline characteristics

The list of the baseline characteristics that we collect to evaluate the population:
GenderAgeHemorrhoid stageThe number of enlarged hemorrhoidsHemorrhoid symptoms

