### Statistics

The ITT analysis included all randomized patients treated for at least 1 week, who were evaluated for efficacy at baseline and at least once at subsequent evaluation points during the study. The PP-analysis will exclude from the full analysis all the non-compliant patients, patients who received incomplete treatment, and patients who refused further treatment after randomization.

Quantitative variables are described as means with standard deviations, medians, range, or interquartile range as appropriate. Categorical variables are described in absolute numbers and percentages. The statistical analysis of the quantitative variables, with independent groups, is performed with the parametric Student’s *t* test, providing that its conditions for application are met. Otherwise, the non-parametric Mann-Whitney *U* test is used. Statistical analysis for categorical variables is performed using the Pearson *χ*^2^ test or the Fisher exact test. Specifically, the above methods are used to compare the two groups in terms of baseline characteristics in order to assess whether the randomization has been effective. Ninety-five percent confidence intervals for the ratio will be reported. In all cases, the level of significance will be the usual 5% (*α* = 0.05).

This study has a low risk of selection bias due to the use of a computer random number generator. Central allocation and the use of sequentially numbered drug containers of identical appearance allow to achieve a low risk of deviations. Performance bias may be considered as having an average risk due to blinding only participants of the study, the personnel is not blinding. Blinding of outcome assessment is ensured, so detection bias is unlikely. Attrition bias could probably appear because of the difficulty of collecting data from patients outside the hospital or the refusal of future treatment and visiting the doctor during follow-up.

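### Baseline significance tests cannot judge whether randomisation worked; describe baseline data by arm, and consider a pre-specified adjusted comparison as a modest gain in precision

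*Protocol article*

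**What the plan says.** All places are in the protocol article.

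- **Statistics.** Student's t or Mann-Whitney for quantitative variables, and Pearson chi-square or Fisher for categorical ones, are used to compare the arms at baseline "in order to assess whether the randomization has been effective". The same paragraph adds "In all cases, the level of significance will be the usual 5"%. No action is attached to a significant baseline difference. The comparison methods named are all unadjusted two-group tests.
- **Baseline characteristics.** Five items are listed: gender, age, hemorrhoid stage, number of enlarged hemorrhoids and symptoms. They are introduced as "The list of the baseline characteristics that we collect to evaluate the population".
- **Surgical technique.** "One, two, or three nodes can be removed per procedure", according to how many are enlarged.
- **Assignment of interventions.** Allocation is 1:1 by computer. No stratification factor is named.
- **The main outcome measures.** The primary outcome is the quantity of opioid per day in the first week. VAS pain is secondary.
- **Sample size.** The calculation rests on the proportion of patients who take an opioid: 20–30% without preemptive analgesia against at most 10% with it, 72 per arm.

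**The concern.** A significance test asks whether a difference is larger than chance would produce. If allocation was random, chance is the only possible source of a baseline difference, so the null hypothesis is true by design. A significant result is then a false alarm. A non-significant one does not show that the arms are alike on variables that matter.

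Two things are at stake, both modest. A reader may take a clean set of p-values as evidence that allocation was sound, or a single small p-value as evidence that it failed. And the number of enlarged hemorrhoids, which is collected before treatment and sets how much tissue is excised, could be used to sharpen the treatment comparison instead of being spent on a test that gives no useful answer.

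**Working it through.** The plan states no figure for this point, so there is none to reproduce. Inputs from the article are five baseline variables, a 5% level, 72 per arm and opioid incidences of 20–30% and 10%. Everything marked as assumed is not in the article.

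**1. False alarms under correct randomisation (independence assumed).** P(at least one p<0.05) = 1 − 0.95^k.
- k = 5: 1 − 0.95^5 = 0.226
- k = 3: 0.143
- k = 8: 0.337 (for example, if symptoms are tested as several items)

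Positive correlation among the variables would lower these values.

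**2. What one test can see (binary factor, assumed prevalence 50%).**
- SD of the difference between arms: sqrt(2 × 0.25/72) = 0.083.
- Difference needed for p<0.05: 1.96 × 0.083 = 0.163, about 16 percentage points.
- Chance of a difference of 10 points or more under correct randomisation: about 21%. Most of these would not be flagged.
- Power to detect a true distortion of 45% against 55%: Phi(0.10/sqrt(2 × 0.45 × 0.55/72) − 1.96) = Phi(−0.75), about 23%.

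**3. Possible gain from adjustment, VAS (assumed effect 0.4 SD, two-sided 5%).** Power = Phi(0.4/sqrt(2(1 − R²)/72) − 1.96), where R² is the assumed share of variance explained by the covariates.
- R² = 0: Phi(0.440) = 67.0%
- R² = 0.1: Phi(0.570) = 71.6%
- R² = 0.2: Phi(0.723) = 76.5%

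**4. Possible gain, any opioid use, 25% against 10%.** Simulated trials with 72 per arm, likelihood-ratio test of treatment with and without stage and number of nodes. The odds ratios are assumed.

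| Odds ratio: stage / per node | Unadjusted | Adjusted | Gain, 2,000 trials | Gain, repeat with 10,000 trials |
|---|---|---|---|---|
| 1.5 / 1.5 | 69.2% | 70.4% | 1.2 points | 1.4 points |
| 2 / 2 | 68.0% | 71.0% | 3.0 points | 2.6 points |
| 3 / 2.5 | 67.4% | 72.2% | 4.8 points | 5.0 points |

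The power columns are from the 2,000-trial runs, where each estimate has a Monte Carlo standard error of about 1 point. The repeat took two stages equally likely and one, two or three nodes equally likely. With covariates of no prognostic value it showed no loss. The gain is therefore about 1.5 to 5 points.

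**5. Room for covariates.** Expected opioid users:
- 20% control rate: 72 × 0.20 + 72 × 0.10 = 21.6
- 25% control rate: 72 × 0.25 + 72 × 0.10 = 25.2

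Treatment plus two covariates makes three parameters, so 21.6/3 = 7.2 to 25.2/3 = 8.4 events each.

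**The case against.** The strongest reply is that little turns on the baseline tests. The article attaches no consequence to them, so they cannot change an efficacy result, and in about 77% of correctly randomised trials (1 − 0.226) none of five independent tests would flag anything. That stands, and it is why the point is minor.

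A second reply is that the argument assumes proper randomisation, which is the very thing being checked. Assignment of interventions has one investigator generating the sequence, enrolling and assigning, so the null hypothesis need not be true if allocation was subverted. In principle that is right. But at 72 per arm a test is a weak detector (about 23% for a 10-point distortion), and whether the sequence was concealed is a matter of process that p-values do not settle.

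The objections to adjustment have more force, and a reader could infer too much here:

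- **That the unadjusted comparison is wrong.** It is not. No stratification factor is named, and a simple two-group comparison in a randomised trial is valid.
- **That leaving out covariates is a defect.** A condensed article commonly leaves covariates to the full protocol or analysis plan, and neither is shown.
- **That stage and number are established predictors of pain.** The Background lists determinants such as wound healing and surgical technique and names neither variable. Number of nodes has indirect support because it sets the extent of excision. Stage has none. The primary outcome is opioid quantity, not pain itself.
- **That the gain is known.** The effect size, R², stage mix and odds ratios are all assumed, and the larger gain is for a secondary outcome.

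**Conclusion.** The baseline-testing point holds in full on the article's own words: the method is stated, its purpose is stated, and the method cannot serve that purpose. The false-alarm figure of about 23% assumes five independent tests; three to eight tests give 14% to 34%.

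Adjustment holds only as a recommendation for precision. It is worth about 1.5 to 5 power points for any opioid use at 25% against 10%, and about 5 to 10 points for VAS if the covariates explain 10–20% of variance, all conditional on assumed prognostic strength. It corrects no invalid analysis. The documents do not support a reading that the treatment comparison is biased or that randomisation failed. Severity is minor.

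**What to change.** 1. In Statistics, delete the baseline significance tests and the phrase about judging randomisation. Present the five baseline characteristics descriptively by arm, with the summaries that section already names.
2. Optionally, pre-specify before unblinding an adjusted comparison using the number of enlarged hemorrhoids and, if wanted, stage, with the unadjusted result alongside. Enter no more than these two covariates.
3. Match the model to the outcome. The primary outcome is opioid quantity per day, and at the planned incidences 70–80% of controls and about 90% of the ketoprofen arm would take none. The model must suit such data; proportional-odds regression, a covariate-adjusted counterpart of the Mann-Whitney test, is one candidate. Keep logistic regression with a standardised risk difference for the proportion with any opioid use, on which the sample size rests. It should not replace the primary outcome without saying so. For VAS, add the covariates to a linear model.
4. If stage is used, first settle its levels: Eligibility criteria give grades III–IV, Recruitment gives stages II–III.

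**Cost.** Item 1 is a change of wording. Item 2 needs no new data, but recruitment began in April 2020, and a changed primary model may count as an amendment to be sent to the ethics committee and uploaded to the registry. The statistical cost is the small number of events, about 22 to 25 opioid users, which is the reason for the limit of two covariates.

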### Data monitoring

There is no data monitoring committee designated for this trial. Any adverse and serious adverse events will be immediately reported to the principal investigator and the primary sponsor. Participants’ names and collected data are subject to medical confidentiality. In cases of withdrawal, collection of data will cease but not be erased. A logistics database with a patient’s complete ID will be used and kept within a separate password-protected system from the results database with all study information. At the end of the trial, the original peri-operative package and database will be archived by the principal investigator, who is responsible for providing data to the trial investigators.

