### Interventions

#### Preoperative preparation

Two hours before the procedure, every patient receives a medication. The research group receives ketoprofen 100 mg per os; the control group receives a placebo.

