### The main outcome measures

The trial is conducted to evaluate the primary outcome: the quantity of the opioid administration intake per day during the first week postoperatively that is necessary to hold pain level no more than 3–4 VAS points in every patient. We use tramadol as an opioid analgesic in a single standard dose of 100 mg for patients with persistent severe pain syndrome in our clinic. The study also assesses the following secondary outcomes: (1) the pain severity before and after defecation according to VAS on the 6, 12, and 24 h after the procedure, then 2 times per day up to 7th postoperative day; (2) duration and (3) frequency of other analgesics intake (systemically and topically) during the first week postoperatively; (4) readmission rate and (5) overall quality of life on the 7th and 30th days; (6) time from the procedure to return to work; and (7) the complications rate (i.e. bleeding, retention of urine, infectious complications) in the early postoperative period (30 days after procedure). The pain severity, duration and frequency of other analgesics intake during the first week postoperatively will be assessed using “Postoperative protocol for pain management” (Additional file 2). The overall quality of life will be assessed with a patient-reported questionnaire Short Form 36 (SF-36). A total score in each of the 8 sections will be calculated and transformed into a 0–100 scale with a score of zero equivalents to maximum disability and a score of 100 equivalents to no disability. Other secondary outcomes will be updated during visits or by phone on the 7 and 30 days after the surgery.

All patients are scheduled to return to the ambulatory clinic on the 7 and 30 days after the surgery. During these visits, postoperative data is collected and digital rectal examination is performed. If a patient fails to follow up, the researcher may contact the patient by all means available (phone, email, or mail) to ascertain whether the patient has had any complications and/or adverse events that were treated at another hospital. If the researcher is unsuccessful in contacting the patient, the patient will be considered as lost to follow-up.

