### Data collection, management, and analysis

All data will be collected prospectively using eCRFs designed for this trial. The reasons for withdrawal will be documented. The investigator will attempt to contact each participant at least 3 times during each follow-up window before declaring them lost for observation. The study exit form will be recorded in the eCRF. All prior data will be analyzed within the research.

All patients will receive clarifications of all the study procedures and will be able to discuss them with the primary investigator. All patient data will be handled according to the principles of doctor–patient confidentiality; the subjects will be anonymized and analyzed with individual identifier numbers transcribed into eCRF.

Data analysis will be performed by one of the researches who is blind to the randomization by using Statistical Product and Service Solutions (SPSS) Statistics for Windows, version 20.0 (IBM Corp., Armonk, NY, USA). Continuous variables will be presented as mean and standard deviation, and categorical variables will be presented as frequency or percentage.

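### The rule that data collection ceases on withdrawal does not separate refusing further treatment or visits from withdrawing consent, so later outcome data can be lost needlessly

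*Protocol article*

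**What the plan says.** All places are in the Protocol article.

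- **Data monitoring** gives one rule without qualification: "In cases of withdrawal, collection of data will cease but not be erased".
- **Data collection, management, and analysis** adds that reasons for withdrawal and a study exit form are recorded, and that "All prior data will be analyzed within the research". For patients who cannot be reached: "The investigator will attempt to contact each participant at least 3 times during each follow-up window before declaring them lost for observation".
- **The main outcome measures** covers missed visits: "the researcher may contact the patient by all means available (phone, email, or mail) to ascertain whether the patient has had any complications" or adverse events treated at another hospital. Other secondary outcomes are updated at a visit or by phone on days 7 and 30.
- **Statistics** defines the main analysis set: "The ITT analysis included all randomized patients treated for at least 1 week, who were evaluated for efficacy at baseline" and at least once afterwards. The per-protocol set leaves out, among others, "patients who refused further treatment after randomization". The same section names as a likely source of attrition bias "the refusal of future treatment and visiting the doctor during follow-up".
- **Preoperative preparation** fixes the randomised treatment: "Two hours before the procedure, every patient receives a medication", either ketoprofen or placebo. No further randomised dose is described.

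**The concern.** A patient can leave a trial in at least three ways: by declining further treatment, by declining visits, or by withdrawing consent to the use of new data. Only the third obliges the investigator to stop collecting. The Data monitoring rule does not say which of them it covers, so site staff can apply it to all three.

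This matters more here than in a trial of continuing treatment. The randomised exposure is complete before the first postoperative outcome is measured. Whatever a patient later declines is shared postoperative care or a visit, and neither changes what was randomised. Outcomes after that point still belong to the randomised comparison, and outcomes that were not collected cannot be recovered by any later analysis.

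**Working it through.** **1. What each rule does to a patient who declines further care on day 2 but does not object to data collection**

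| Section | Effect on this patient |
|---|---|
| Data monitoring | If recorded as withdrawn: nothing is collected after day 2; days 0 to 2 are kept |
| Data collection, management, and analysis | Data up to day 2 are to be analysed |
| Statistics, ITT set | Appears to fail the one-week treatment condition, so is left out |
| Statistics, per-protocol set | Left out |

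The second and third rows do not fit together: the earlier data are to be analysed, but the main analysis set has no place for the patient. The one-week condition is also hard to apply to a single dose. It has meaning only if the shared postoperative analgesics count as treatment.

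**2. What could be lost after day 2, and what could still be obtained**

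- Opioid use per day to day 7 (primary outcome) and other analgesic use: in the ward record until the usual discharge on day 4–5, then from the patient.
- Pain scores to day 7: need the patient's cooperation.
- Readmission, complications to 30 days and return to work: from the chart or the day 7 and day 30 contacts already planned.
- Quality of life on days 7 and 30: needs the patient's cooperation.

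A good part of the loss is therefore avoidable without further trial treatment, though not all of it.

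**3. Size, by illustration only**

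The plan states no withdrawal rate and no dropout allowance, so there is no planned figure on this point to reproduce. Inputs from the Sample size section: opioid use of 20 to 30% without preemptive analgesia (30% used here), 10% or less with it (10% used), and 72 per arm. The withdrawal inputs below are assumptions.

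*Bias.* Let p be the true opioid rate in an arm, w the share that withdraws before any opioid use is recorded and is left out, and q the opioid rate those patients would have had. The observed rate is (p − w·q)/(1 − w).

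Control arm, p = 0.30, w = 0.10:
- q = 0.30: (0.30 − 0.03)/0.90 = 30.0%, no bias
- q = 0.50: (0.30 − 0.05)/0.90 = 27.8%
- q = 0.80: (0.30 − 0.08)/0.90 = 24.4%

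With the ketoprofen arm complete at 10%, the true difference of 20 points is observed as 20.0, 17.8 or 14.4 points. If the ketoprofen arm also loses 10% with q = 0.50, its rate becomes (0.10 − 0.05)/0.90 = 5.6%. The difference is then 27.8 − 5.6 = 22.2 points, larger than the truth. The direction depends on who withdraws, and the documents do not say.

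*Precision.* If every withdrawn patient is left out, 72 per arm becomes 72 × 0.95 = 68.4, 72 × 0.90 = 64.8 or 72 × 0.80 = 57.6. Two-sided power at 5% for 30% v 10%, without continuity correction, comes from z = (0.20·√n − 1.96·√(2·0.20·0.80))/√(0.30·0.70 + 0.10·0.90). It falls from 85.9% to 84.0%, 82.0% and 77.2%. This loss is modest; the possible bias matters more.

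**The case against.** The strongest reply is that withdrawal in the Data monitoring section means withdrawal of participation or consent. The sentence stands among statements on confidentiality and storage of identifiers, and stopping collection while keeping existing data is then normal practice. The Statistics section lists refusal of further treatment as a per-protocol exclusion, not as withdrawal. Missed visits have their own contact rules. The article also condenses a full protocol and a consent form that are not shown, and grades of withdrawal are often set out there.

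Much of this stands, and it rules out several stronger readings that a reader might infer:

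- *That refusing treatment or visits triggers the rule.* This is an inference; the article never says so.
- *That the trial loses its opioid, pain and safety data for these patients.* Only data after withdrawal are at risk. Earlier data are kept, and much of the first week falls within the usual inpatient stay.
- *That only the earlier data are analysed, with later days counted as zero opioid use.* Neither is written. Scoring an early withdrawer as zero would also conflict with the one-week ITT condition.
- *That an early record is bound to show no opioid.* The Postoperative period section mentions an opioid on day 5, but the main outcome section counts opioid intake per day through the first week and sets no such day.
- *That the bias has a known direction.* It would need evidence on who withdraws from each arm, and there is none.

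The objection does not remove the point. The unqualified stop and the one-week ITT condition are positive statements in the article, not details left to another document. The contact rules protect patients who fail to attend, not those recorded as withdrawn. The protocol itself foresees refusal of treatment and visits as a cause of attrition.

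**Conclusion.** The point holds in a limited form. The withdrawal rule does not distinguish declining care from withdrawing consent to data collection. Read literally, it can end follow-up for patients whose outcomes could properly have been recorded, and the ITT definition would then probably remove those who leave in the first week.

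The data at risk are those after withdrawal: the remainder of the first-week opioid and pain record, and 30-day complications, readmission and quality of life. The effect on the result cannot be sized from the documents. The illustrations rest on assumed withdrawal shares and assumed opioid need among those who leave. They use proportions of opioid users, as the Sample size section does, whereas the primary outcome is worded as a quantity per day. The point is a cheap improvement to what is collected and does not show that the trial's result will be wrong.

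**What to change.** 1. In Data monitoring, replace the single sentence with two rules. (a) A patient who declines further treatment or visits remains in follow-up: chart data and the existing day 7 and day 30 contacts continue, and the data are analysed in the randomised arm. (b) Collection stops only when the patient explicitly withdraws consent to data collection, with date and reason recorded; data collected up to then are kept.
2. In Statistics, remove the one-week treatment condition from the ITT set, so that these patients are analysed as randomised. Rule (a) alone would not achieve this.
3. Align the sentence on earlier data in Data collection, management, and analysis with both changes.

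Cost: a short amendment, a line in the consent form and some extra phone calls. The chart review, exit form and day 7 and day 30 contacts are already planned, and no clinical rule changes. Pain scores after discharge and quality of life will still be missing for patients who decline to answer.
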